**Methods/Design:**

This trial compares Mindfulness-Based Cognitive Therapy (MBCT), a novel form of treatment combining mindfulness meditation and cognitive therapy for depression, with both Cognitive Psycho-Education (CPE), an equally plausible cognitive treatment but without meditation, and treatment as usual (TAU). It will test whether MBCT reduces the risk of relapse in recurrently depressed patients and the incidence of suicidal symptoms in those with a history of suicidality who do relapse. It recruits participants, screens them by telephone for main inclusion and exclusion criteria and, if they are eligible, invites them to a pre-treatment session to assess eligibility in more detail. This trial allocates eligible participants at random between MBCT and TAU, CPE and TAU, and TAU alone in a ratio of 2:2:1, stratified by presence of suicidal ideation or behaviour and current anti-depressant use. We aim to recruit sufficient participants to allow for retention of 300 following attrition. We deliver both active treatments in groups meeting for two hours every week for eight weeks. We shall estimate effects on rates of relapse and suicidal symptoms over 12 months following treatment and assess clinical status immediately after treatment, and three, six, nine and twelve months thereafter.

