## Trial Objectives and Purpose

The objectives of this trial are to test whether Mindfulness-Based Cognitive Therapy (MBCT), a novel form of treatment combining mindfulness meditation and cognitive therapy for depression delivered in addition to treatment as usual (TAU), will reduce the risk of relapse to Major Depression in recurrently depressed patients and the incidence of suicidal symptoms in those with a history of suicidality who relapse. To this end we aim to compare MBCT with both TAU alone and Cognitive Psycho-Education (CPE), an equally plausible cognitive treatment, but without meditation.

Thus the study uses a "dismantling" paradigm in the sense that it removes meditation - the component of MBCT, the main treatment under investigation, that we hypothesize to be effective - to form CPE, the comparison treatment, which is otherwise identical in its content. Removal of the meditation component of MBCT from CPE allows us to assess, for the first time, the added benefits of the meditation component of MBCT in preventing relapse in people with a history of recurrent depression.

The study is also investigating potential mediators and moderators of treatment outcome by assessing symptoms, stressful life events, and aspects of cognitive functioning related to risk of relapse to depression - before and after treatment and during the follow-up period.

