### Outcome Measures

The primary outcome measure of the trial is the time to relapse or recurrence meeting DSM-IV criteria for Major Depression, which we assess by the Structured Clinical Interview for DSM-IV (SCID). We assess the occurrence of relapse or recurrence at all follow-up assessments, and treat 'return to treatment' as a relapse or recurrence if, in the judgment of a blind assessor, the participant has experienced exacerbation of symptoms that would have met the criteria for Major Depression in the absence of immediate treatment. In addition to diagnostic status, we assess severity of depression and hopelessness at all time points, using several interview and self-completed measures including the Hamilton Rating Scale for Depression, the Beck Depression Inventory and the Beck Hopelessness Scale. These quantitative measures strengthen the dichotomised outcome of diagnosis. The statistical analysis plan in Appendix 1 gives further details.

We assess cognitive measures relevant to risk of relapse or recurrence, namely mindfulness, self-compassion, rumination, self discrepancy, autobiographical memory and executive capacity before and immediately after treatment and at the end of the follow-up. We shall use these measures in explanatory analysis of factors that mediate or moderate efficacy.

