### Analysis

We shall analyse all data by intention to treat. We shall use Cox regression, a form of survival analysis that takes account of covariates, to analyse relapse and recurrence. We shall analyse most other measured variables by mixed-model analysis of variance (ANOVA). We shall use baseline values of the dependent variable as a covariate in all analyses; we shall use other baseline measures or demographic characteristics as covariates when they contribute significantly to the analysis. We shall use multi-level modeling to take account of the clustering of participants within classes within centres. To minimise testing, we shall combine measured outcomes at different time points using the 'area under (the resulting) curve'. We shall use cognitive measures to explore the extent to which they mediate relapse and recurrence during treatment and follow up. Similarly we shall use data at each time-point on the Beck Scale for Suicide Ideation to explore the extent to which the cognitive measures mediate the occurrence of suicidality over the follow-up period, again analysing 'area under the curve'. Additionally we shall examine recurrence of suicidality specifically for those participants who relapse to Major Depression (MDD) and had a history of suicidal ideation or behaviour at entry to the trial. We predict that, all else being equal, suicidal ideation will fall in those who have received treatment with MBCT. Further details of the data analysis plans are given in Appendix 1.

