Recurrence of suicidal ideation, both within episodes of major depression and over the follow-up period, is an important secondary outcome. Initially we shall examine recurrence of suicidality specifically for those participants who relapse to Major Depression and had a history of suicidal ideation or behaviour at entry to the trial. Then we shall compare severity of suicidal symptoms, as measured by the Beck Scale for Suicide Ideation (BSS current) and the MINI suicide-tracking measure, across the follow-up period for all participants, whether or not they relapsed or became suicidal. Finally we shall compare suicidal cognitions (and ability to let go of cognitions that occur), at baseline, T1 and T5 only between groups using AnCova, with T0 as covariate and T1 and T5 as separate outcomes.

By assessing cognitive measures relevant to risk of relapse to depression, namely mindfulness, suppression, self-compassion, rumination, self guides, autobiographical memory and executive capacity, before and immediately after treatment and at the end of follow-up, we can use them in an explanatory analysis to study factors that mediate efficacy. We shall use regression analysis (binary logistic regression for the dichotomous outcome of relapse and linear regression for the worst HRSD score during follow-up) to explore whether the change from T0 to T1 in each of these measures can account for the effects of treatment on risk of relapse.

Where necessary we shall transform variables closer to Normal distributions for AnCova. Where data are missing, we shall use data from alternative sources, notably therapists on the trial and referring general practitioners. We shall also use sensitivity analysis to assess the effect of including participants whose data on relapse is collected by these means.

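### The suicidality objective, and the first-listed analysis for it, are confined to participants who relapse, so the arms compared are no longer randomised groups

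*Protocol article*

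**What the plan says.** All references are to the protocol article.

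- **Trial Objectives and Purpose** asks whether MBCT reduces relapse and also "the incidence of suicidal symptoms in those with a history of suicidality who relapse". The Methods/Design part of the abstract repeats this: "the incidence of suicidal symptoms in those with a history of suicidality who do relapse".
- **Outcome Measures** fixes the primary endpoint: "The primary outcome measure of the trial is the time to relapse or recurrence meeting DSM-IV criteria for Major Depression".
- **Appendix 1** says that recurrence of suicidal ideation, "both within episodes of major depression and over the follow-up period, is an important secondary outcome". It then lists three analyses in order. The first is to "examine recurrence of suicidality specifically for those participants who relapse to Major Depression", limited to people whose suicidality predates the trial. The second compares severity on the BSS and the MINI measure "across the follow-up period for all participants, whether or not they relapsed or became suicidal". The third compares suicidal cognitions between groups at T1 and T5.
- **Analysis** also describes the relapser analysis, but introduces it as an addition to the analyses of suicidal ideation over follow-up.
- **Sample Size** plans relapse at 39% (MBCT), 57% (CPE, for power; 59% is expected) and 70% (TAU), with 120, 120 and 60 participants.

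The text gives no caution about, or adjustment for, selection on relapse.

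**The concern.** Two restrictions define the first analysis, and they differ in kind. History of suicidality is a baseline fact and a stratification factor, so restricting to it keeps the randomised comparison. Relapse is an event after randomisation that MBCT is meant to prevent. If MBCT works as planned, the people who still relapse under MBCT have been selected by a different process from those who relapse under TAU, and nothing makes the two sets alike in their prior risk of becoming suicidal.

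A difference in suicidality between these sets mixes any effect of treatment on suicidality during an episode with a difference in who is left. If MBCT mainly prevents relapse in lower-risk people, its remaining relapsers will look more suicidal without any harm. If it mainly prevents relapse in higher-risk people, they will look less suicidal without any benefit beyond relapse prevention. As this is a named treatment objective, a reader would take the contrast as an effect of MBCT.

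**Working it through.** **1. Inputs.** Arm sizes and relapse rates come from Sample Size. The article gives no figure for the suicidality analysis, so the only figures of its own to reproduce are the power statements that use these rates. With HR = ln(1−p₁)/ln(1−p₂), d = expected events, a = share allocated to MBCT and two-sided 5%, power = Φ(|ln HR|·√(d·a·(1−a)) − 1.96).

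- MBCT v TAU: HR = ln 0.61/ln 0.30 = 0.411; d = 46.8 + 42 = 88.8; a = 2/3; power 97.7% (stated 99%).
- MBCT v CPE: HR = ln 0.61/ln 0.43 = 0.586; d = 46.8 + 68.4 = 115.2; a = 1/2; power 81.9% (stated 80%).

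Both are within 2 points of the stated values, so these are the rates on which the plan rests.

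**2. Who is left after conditioning on relapse.**

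| Arm | Randomised groups in final sample | Relapse | Relapsers | Left out |
|---|---|---|---|---|
| MBCT | 120 | 39% | 46.8, about 47 | 61% |
| CPE | 120 | 57% | 68.4, about 68 | 43% |
| TAU | 60 | 70% | 42 | 30% |

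At the expected 59%, CPE has 120 × 0.59 = 70.8 relapsers. The article does not say what share has a suicidal history. If it is 70% (assumption; range 50% to 90%), and the overall relapse rates also hold in that subgroup (a further assumption), about 33 MBCT (23 to 42), 48 CPE (34 to 62) and 29 TAU (21 to 38) enter the analysis.

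**3. Can the contrast move with no effect on suicidality given relapse?** All inputs here except the overall 70% and 39% are assumed. Half the participants are high-risk and half low-risk. Once relapsed, 60% of high-risk and 20% of low-risk people become suicidal, whatever their arm. TAU relapse is 90% and 50%, which averages 70%.

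- TAU, all randomised: 0.5 × 0.9 × 0.6 + 0.5 × 0.5 × 0.2 = 0.32. Among relapsers: 0.32/0.70 = 46%.
- MBCT relapse averages 39% in every row below.

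| MBCT relapse, high/low risk | All randomised: MBCT v TAU | Relapsers only: MBCT v TAU |
|---|---|---|
| 70% / 8% | 22% v 32% | 0.218/0.39 = 56% v 46% |
| 60% / 18% | 20% v 32% | 0.198/0.39 = 51% v 46% |
| 50% / 28% (proportional) | 18% v 32% | 0.178/0.39 = 46% v 46% |
| 39% / 39% | 16% v 32% | 0.156/0.39 = 40% v 46% |

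In each row MBCT lowers suicidal relapse among all randomised, and suicidality given relapse is equal by construction within each risk stratum. The relapser contrast nevertheless points against MBCT, nowhere, or in its favour.

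**4. Theoretical bounds.** Let half of TAU relapse be suicidal (assumption), that is 35% of all TAU participants. If all 31 points of prevention fall on non-suicidal relapse, the MBCT figure is 35/39 = 90% v 50%. If all fall on suicidal relapse, it is (35 − 31)/39 = 10% v 50%.

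**The case against.** The strongest reply is that this is one secondary analysis among several. The main text introduces it as additional, Appendix 1 says that it will examine relapsers but compare severity in all participants, and no error rate or power is assigned to it. The all-participant BSS and MINI comparison keeps the randomised groups, and the BSS area under the curve is adjusted for baseline and the stratification variables. Whether suicidality returns when depression returns is also a fair descriptive question.

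Most of this stands. It limits the damage but does not remove the problem. The abstract and the objectives section state the relapser question as something that MBCT is tested on, so an arm comparison is implied, and Appendix 1 lists that analysis first. The all-participant comparison measures severity, including in people with no suicidal history, and leaves the incidence objective to be reported from the selected subset.

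Three stronger readings are tempting and not supported:

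- A reader might infer that the trial's whole suicidality question would be answered in the wrong direction. It would not, because a comparison that preserves randomisation is also planned.
- A reader might infer a separate breach of intention to treat. Nothing says that anyone is analysed outside the allocated arm, so this would only be another name for the same selection problem.
- A reader might take 90% or 10% v 50% as the likely size. These need all prevention to fall on one kind of relapse, and they apply overall relapse rates to the suicidal-history subgroup. Nothing in the article supports the pattern behind 90%. The section on the interventions argues, if anything, for particular benefit in people with past suicidal depression.

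**Conclusion.** The point holds for the suicidality objective and for the first-listed analysis that serves it. On the plan's own rates, conditioning on relapse drops 61% of MBCT, 43% of CPE and 30% of TAU for a reason that treatment is meant to affect, and the remaining contrast is not protected by randomisation.

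The size and direction of the bias cannot be known from the article. Under the assumed strata, relapser suicidality is 40% to 56% for MBCT against 46% for TAU, with no effect on suicidality given relapse. That range depends on the assumed 50:50 risk split, the 60% and 20% suicidality rates, and overall relapse rates that apply to the people analysed. The retained counts and the loss of comparability do not depend on the assumed strata. The primary relapse analysis, its power and the all-participant severity comparison are unaffected.

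**What to change.** 1. Make the main analysis for this objective cover all randomised participants with a history of suicidality at entry. The outcome is time to first relapse accompanied by suicidality, with treatment group and the stratification variables as predictors. Participants lost to follow-up are censored at their last observation, as Appendix 1 already does for relapse. Do not count everyone without a recorded relapse as event-free, because that would misclassify people lost before relapse, and 20% attrition is expected.
2. State that a participant whose first relapse is without suicidality stays at risk for a later one. Appendix 1's rule that only the first relapse counts was written for the primary endpoint.
3. Keep the all-participant BSS and MINI comparison, since it also captures suicidality outside a major depressive episode.
4. Label the relapser-only analysis descriptive, with no causal claim, and reword the objective in the abstract and in Trial Objectives and Purpose to match.

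The cost is wording in the objectives and the analysis plan, settled before analysis. Suicidal history is already a stratification factor, and episode onset is already dated by interview. There are two downsides. Episodes that resolve between visits can be classified as suicidal or not only from the retrospective interview data already collected, because the BSS records current ideation at assessments. And the question of suicidality given relapse can then be described but not tested as a treatment effect.

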### Post-Treatment Assessment and Follow-Ups

Once treatment is finished, we invite all participants to a post-treatment assessment. Over the following 12 months we invite them to attend research assessments at three, six, nine and twelve months after treatment. We also invite those allocated to treatment with MBCT or CPE to attend two treatment sessions, one 6-8 weeks, the other six months after treatment. At post-treatment assessment (T1), we use the SCID mood disorder module to assess current diagnostic status and any changes in that status over the treatment phase. We ask participants to repeat the cognitive tasks and questionnaires they completed during the pre-treatment assessments with the exception of the Childhood Trauma Questionnaire (CTQ), the worst ever BSS, the crisis card, and questions about sociodemographic status. The follow up assessments at three (T2), six (T3) and nine months (T4) consist of a SCID mood disorder module, the Hamilton Rating Scale for Depression and, when there has been suicidal behaviour or self harm, the SASII assessment, focusing on the time since the last assessment. We also ask them to complete questionnaires assessing current symptoms and history of treatment since last assessment (BSS current, Suicide Cognitions Questionnaire, MINI Suicidality Tracking, BDI-II, BHS, Life Events Questionnaire, CORE, Euro-QOL, PHQ9, GAD7). During the final follow-up assessment (T5), we ask participants to complete the same measures as at the T1 assessment. Additional File 1 includes a table summarizing all these baseline and follow-up assessments.

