## Appendix 1: Statistical Analysis Plan

The primary outcome measure will be the time to relapse or recurrence meeting DSM-IV criteria for a major depressive episode (American Psychiatric Association, 1994) on the Structured Clinical Interview for DSM-IV (SCID, Spitzer et al., 1992). Occurrence of relapse or recurrence will be assessed after treatment (T1), and at three (T2), six (T3), nine (T4) and twelve (T5) months thereafter by trained psychologists blind to participants' treatment condition. If the interview establishes that symptoms meeting diagnostic criteria for major depression have been present since the last assessment, we shall ask participants when this episode of depression started (and ended, if they are no longer symptomatic). 'Return to treatment' will also be treated as a relapse or recurrence if, in the judgment of a blind rater, the participant experienced exacerbation of their symptoms that would have met the criteria for Major Depression in the absence of immediate treatment.

The analysis will be by 'intention to treat' (ITT). The time (in weeks) of relapse or recurrence to Major Depression, as defined above, will be the dependent variable in survival analysis. The treatment group and stratification variables will be used as predictors.

For participants who are lost from the trial we shall use their available measures and then censor them at the time of their last observation. Since only a participant's first relapse or recurrence to Major Depression will contribute to the survival analysis, the subsequent loss of that participant will not affect the analysis.

Participants who miss one or more follow-up assessments, but are then assessed at a later time point will be asked whether they have experienced a relapse or recurrence according to SCID diagnostic criteria since the last assessment, including time periods which would have been covered in missed assessments. This will enable us to assess the time to relapse and thus to censoring.

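### The mediation analysis lets relapses that began before T1 be explained by change measured at T1, so the effect of an early relapse can be read as its cause

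*Protocol article*

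**What the plan says.** Appendix 1 of the protocol article (Statistical Analysis Plan) fixes mediator, model and outcome. The mediator is the change in each cognitive measure from before to just after treatment: the trial will "explore whether the change from T0 to T1 in each of these measures can account for the effects of treatment" on risk of relapse. The models are "binary logistic regression for the dichotomous outcome of relapse and linear regression for the worst HRSD score during follow-up".

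The Analysis section gives the window. It will use the cognitive measures to "explore the extent to which they mediate relapse and recurrence during treatment and follow up".

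Two further places show that relapses before T1 are counted:

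- Appendix 1, on the primary outcome: "Occurrence of relapse or recurrence will be assessed after treatment (T1), and at three (T2), six (T3), nine (T4) and twelve (T5) months thereafter". Participants with an episode are asked when it started.
- Post-Treatment Assessment and Follow-Ups, on T1: "we use the SCID mood disorder module to assess current diagnostic status and any changes in that status over the treatment phase". The mediators are taken at the same assessment: "We ask participants to repeat the cognitive tasks and questionnaires they completed during the pre-treatment assessments", with a few listed exceptions that are not cognitive mediators.

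The article does not limit the mediation analysis to relapses that start after T1.

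**The concern.** Mediation needs the mediator to come before the outcome. For a relapse during the 8-week course the order is reversed: the episode starts first, and mindfulness, rumination and the rest are measured afterwards. A current or recent episode may itself worsen those scores. A regression of relapse on the T0-T1 change would then find that people whose scores worsened relapsed more often. If the treatment also improves the measure on average, the two results together look like a mechanism even where the measure has no influence on relapse.

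The Trial Objectives name mediators as something the study investigates, and the Discussion makes identifying the critical therapeutic factors one of two aims. A false mechanism would bear directly on that aim.

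**Working it through.** **Inputs.** From Sample Size: relapse 39% (MBCT), 57% (CPE, the figure used for power; 59% is the expected rate) and 70% (TAU); final sample 120, 120 and 60. From the Abstract: 8 weeks of treatment and 12 months of follow-up, so 8 + 52 = 60 weeks. Assumed, because the article gives no figure: constant hazard, the period to which the rates apply, the treatment effect on a mediator, and the shift that an early episode causes in the T1 score.

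**The plan's own figures.** The mediation analysis has none. The relapse rates do reproduce the stated power. For MBCT v CPE, HR = ln(0.61)/ln(0.43) = 0.586 and events = 120 × (0.39 + 0.57) = 115.2. Freedman's formula gives z = √115.2 × (1 − 0.586)/(1 + 0.586) − 1.96 = 0.84, so power is 0.80 (stated 80%). For MBCT v TAU, HR = 0.411 with 88.8 events gives 0.977 to 0.982 by two methods (stated 99%).

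**Relapses before T1.** Under a constant hazard the proportion relapsing in the first 8 of 60 weeks is 1 − (1 − p)^(8/60):

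| Arm | p | Before T1 | Number before T1 | All relapses | Share |
|---|---|---|---|---|---|
| MBCT | 0.39 | 0.064 | 7.7 | 46.8 | 16% |
| CPE | 0.57 | 0.106 | 12.8 | 68.4 | 19% |
| TAU | 0.70 | 0.148 | 8.9 | 42.0 | 21% |

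The total is 29.4 of 157.2, or 19%. With 59% for CPE the proportion is 0.112, still about 11%. If the rates apply to the 52 weeks after treatment, the shares are 17%, 20% and 23%.

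**Simulation.** Relapse times were exponential at these hazards. The change score was the arm effect plus a standard normal error, worsened by a fixed shift in anyone relapsing before week 8. The mediator had no effect on relapse. Relapse by week 60 was regressed on arm and change score (logistic), and the change score on arm (linear). False mediation means that both paths were significant at two-sided 5% in the expected direction.

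| Scenario | Shift 0.5 SD | 1.0 SD | 1.5 SD |
|---|---|---|---|
| MBCT v TAU, treatment moves mediator 0.5 SD | 8% | 19% | 31% |
| MBCT v CPE, treatment moves mediator 0.5 SD | 10% | 24-25% | 43-47% |
| MBCT v TAU, treatment does not move mediator | 0.4% | 1.5% | about 4% |
| MBCT v CPE, treatment does not move mediator | 0.2% | 1.5% | 3.4% |

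Ranges within a cell are the spread between separate runs. With the 0.5 SD treatment effect, restricting to participants relapse-free at T1 returned false mediation to about 2% at every shift. That is the nominal level for one path tested in one direction when the other is nearly always significant.

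**The case against.** **The window.** The Abstract speaks of effects over the 12 months following treatment, which could be read as excluding earlier relapses. It does not do so for mediation: the Analysis section names the treatment phase for this very analysis, and Appendix 1 counts relapse found at T1.

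**The size rests on assumptions.** This stands. The Sample Size section ties its rates to no period. A constant hazard gives MBCT its full benefit from the first week; if benefit builds over the course, the arms differ less before T1. Entry requires remission over the previous 8 weeks, so a constant hazard from entry is not established either. No figure in the article supports the 0.5-1.5 SD shift or the 0.5 SD effect on the mediator.

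**An association is not mediation.** This also stands. For MBCT v TAU the mediator-relapse association alone is significant in about 9%, 20% and 35% of simulated trials (about 5% when relapse must follow T1). A reader might take those as false-mediation rates, but both paths are needed, and without a treatment effect on the mediator the rate is 4% or less.

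**The logistic model.** A reader might infer that ignoring censoring produces the reverse causation. It does not: a Cox model counting the same early relapses would have the same fault. Loss to follow-up is a separate and smaller matter. With 20% loss in both arms and 39% v 57% relapse, the odds ratio is 0.51 (losses coded as no relapse) or 0.48 (losses dropped), against a true 0.48. Material bias needs unequal loss: with no true effect, 30% v 10% loss gives 0.82 or 1.16. Appendix 1 partly covers loss by asking about missed periods at later interviews, seeking data from therapists and general practitioners, and adding a sensitivity analysis.

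**Worst HRSD.** A reader might extend the criticism to this outcome. The article defines it over follow-up, which it treats separately from the T1 assessment, so the timing fault is not clearly present. Replacing a worst score by an average would be largely preference.

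**Conclusion.** The point holds as one about timing. The stated rules let the outcome precede the mediator in the mediation analysis of relapse, and nothing in the article prevents it. Under a constant hazard about one relapse in five is affected. The risk of a false mechanism is then material, from about 8% up to 31% (MBCT v TAU) or 47% (MBCT v CPE), but only for measures that the treatment changes and only under the assumed shifts. Those measures are the ones most likely to be reported as mechanisms.

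The existence of the fault is certain from the text; its size is illustrative. The analysis is exploratory, and a reader should not infer that the primary Cox analysis is compromised: it does not use the mediators. The change should be made, but the trial's main conclusion does not depend on it.

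**What to change.** Amend the Analysis section and the mediation paragraph of Appendix 1 together:

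- Include in the mediation analysis of relapse only participants relapse-free at T1, and count first relapses that start after T1, using the onset dates already collected.
- Adjust for the baseline value of the mediator, baseline HRSD and the stratification variables.
- Preferably model time from T1 by Cox regression with censoring at last observation, as in the primary analysis. This is a secondary gain in handling loss; the restriction to relapses after T1 is what removes the reversed order.
- Report the version with all relapses only as a sensitivity analysis.

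The change needs wording and no new data. Three costs should be stated in the plan. The in-treatment relapses, about 6-15% of each arm under the assumptions above, drop out of this analysis. Being relapse-free at T1 is a post-randomisation selection that may differ by arm, so the comparison is no longer strictly the randomised one. The analysis also remains exploratory, since correct ordering does not by itself remove confounding between mediator and relapse.

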### Pre-Class Interviews

We tell all participants the outcome of randomisation by letter (in addition to email or telephone if requested). We invite those allocated to MBCT or CPE to meet the therapist running their class and those in TAU to meet another member of the research team. These meetings take between 1 and 1.5 hours and either prepare participants for classes, including discussion of ways of coping with barriers to treatment, or discuss procedures for keeping in touch with participants not in classes.

Each week of the eight-week treatment phase, we ask all participants to complete a brief set of tracking questionnaires. These include short ratings of tendencies to ruminate, occurrence of intrusive thoughts, thought suppression, and the PHQ9 and GAD7 scales for assessing symptoms of depression and anxiety. At the start of the second class we also ask participants receiving MBCT or CPE to rate the plausibility of their treatment. Finally participants receiving MBCT complete a short diary documenting homework and practice completed throughout the week.

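### Trial therapists may supply missing relapse data with no stated blind adjudication, no link to the censoring rule and no statement of which dataset is primary

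*Protocol article*

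**What the plan says.** Appendix 1 (Statistical Analysis Plan) of the protocol article defines the endpoint: "The primary outcome measure will be the time to relapse or recurrence meeting DSM-IV criteria for a major depressive episode", based on the SCID. It is assessed after treatment and at three, six, nine and twelve "months thereafter by trained psychologists blind to participants' treatment condition". Return to treatment counts as relapse only on a blind rater's judgment. For participants lost from the trial, the plan is to use what is available and then "censor them at the time of their last observation".

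The last paragraph of the appendix adds: "Where data are missing, we shall use data from alternative sources, notably therapists on the trial and referring general practitioners". It continues: "We shall also use sensitivity analysis to assess the effect of including participants whose data on relapse is collected by these means". The second sentence makes clear that the outside sources can supply relapse data.

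Four other sections bear on this:

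- The Interventions: four therapists deliver both MBCT and CPE, each leading six classes.
- Pre-Class Interviews: participants in the two active arms meet their class therapist, and "those in TAU to meet another member of the research team".
- Post-Treatment Assessment and Follow-Ups: two later treatment sessions, at 6-8 weeks and six months, are offered to MBCT and CPE only.
- Inclusion criteria: consent from the participant's GP is required in every arm.

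**The concern.** The primary endpoint is protected by blind SCID assessment and a blind rater. The missing-data rule opens a second route into the same endpoint, and no blinding is stated for it.

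Therapists necessarily know which treatment they gave. The Interventions section takes therapist allegiance seriously enough to plan a check for it, yet the same people may report outcomes. TAU has no therapist, so this source exists in two arms out of three. The last scheduled therapist contact is six months after treatment, while follow-up runs to twelve.

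Three things are left open: who classifies an outside report against DSM-IV criteria and dates its onset in weeks, whether a report extends follow-up past the point where the participant would be censored, and which version of the Cox analysis is primary. If the last is not fixed beforehand, it could be chosen after the results are known.

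**Working it through.** **1. The plan's own figures.** Inputs from Sample Size: 39%, 57% and 70% relapse in MBCT, CPE and TAU; 120, 120 and 60 participants; 5% level (two-sided assumed); 20% attrition.

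- MBCT vs TAU: HR = ln(0.61)/ln(0.30) = 0.411; events = 120×0.39 + 60×0.70 = 88.8. Freedman log-rank with 2:1 allocation: z = √(2×88.8)×(1−0.411)/(1+2×0.411) − 1.96 = 2.35, power 99.1% (stated 99%).
- MBCT vs CPE: HR = ln(0.61)/ln(0.43) = 0.586; events = 120×0.39 + 120×0.57 = 115.2. z = √115.2×(1−0.586)/(1+0.586) − 1.96 = 0.84, power 80.1% (stated 80%).
- Recruitment: 300/0.8 = 375, as stated.

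These reproduce, and this point does not affect them.

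**2. The two rules side by side.** They can be read in sequence (ask other sources, then censor if none answers) or as rivals (censor at the last blind SCID, whatever others report). The text supports either reading, and they give different event counts and follow-up times.

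**3. Worst-case illustration of direction.** Assumptions that are not in the document: 375 splits 150/150/75; 20% of each arm is lost (30/30/15); no relapse was seen before loss; every lost active-arm participant is referred to a therapist, who detects a fraction s of relapses; lost TAU participants contribute nothing; true relapse is p = 57% in every arm, so the true HR is 1.

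- Rule A, no known relapse is counted as relapse-free: recorded rate = 0.8p + 0.2ps.
- Rule B, only reported relapses are added and the rest drop out: recorded rate = (0.8p + 0.2ps)/(0.8 + 0.2ps).
- HR vs TAU = ln(1 − recorded rate)/ln(1 − 0.57).

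| s | Rule A rate | Rule A HR | Rule B rate | Rule B HR |
|---|---|---|---|---|
| 0.25 | 48% | 0.79 | 58% | 1.04 |
| 0.50 | 51% | 0.85 | 60% | 1.08 |
| 0.75 | 54% | 0.92 | 61% | 1.12 |
| 1.00 | 57% | 1.00 | 62% | 1.16 |

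At s = 0.5, Rule A gives 0.456 + 0.057 = 0.513, and Rule B gives 0.513/0.857 = 0.599. The two rules push in opposite directions, and the document does not choose between them. Under Rule A, the approximate two-sided type I error for 150 active vs 60 TAU participants is 7%, 12% and 20% at s = 0.75, 0.5 and 0.25.

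**4. MBCT vs CPE.** Take Rule A with equal detection in both arms and the planned rates. At s = 0.5 the rates are 35.1% and 51.3%, a difference of 16.2 points instead of 18, with HR = ln(0.649)/ln(0.487) = 0.60 instead of 0.586. At s = 0.3 they are 33.5% and 49.0%, a difference of 15.5 points and HR 0.61. The shift is small and toward the null. With equal true rates and equal detection there is no spurious difference. One arises only if detection or reporting differs by arm: with a true rate of 57% in both, detection of 0.5 in MBCT and 0.75 in CPE gives HR 0.92 and about 8% type I error.

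**The case against.** The case for leaving the text alone has real content.

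- GPs are named beside therapists and could cover every arm. This narrows the asymmetry but does not close it: the text says referring GPs, and Referral and recruitment shows that participants also come through advertisements.
- TAU is not without contact. Pre-Class Interviews and the Discussion say the team keeps in touch with that arm. But the missing-data rule does not name that contact as a source, and it is not equivalent to a treating therapist.
- MBCT and CPE share therapists, so source availability does not differ between them. This stands.
- Loss of data is limited by other provisions: those who stop trial treatment are asked to keep attending or give minimal data, and a later SCID covers missed periods. This stands, and it means far fewer than 20% may need outside data.
- A sensitivity analysis on including these participants is promised. It mitigates, but the sentence before it is an unconditional statement of use, and neither says which result leads.

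A reader might go further and infer that the rule lowers relapse in MBCT and CPE by some 4 to 8 points and so favours them over TAU. The document does not support that. It depends on counting a therapist's silence as relapse-free, which is nowhere stated, and on filling every lost participant from therapists while TAU gets nothing from GPs. A therapist who knows nothing may simply supply no data, and censoring then applies. Setting such single-arm shifts against the 18-point MBCT-CPE difference would also mislead, since that difference itself moves only to about 16 points.

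**Conclusion.** The point holds as an unreconciled rule for the primary endpoint. Relapse data may come from unblinded therapists who exist in only two arms, with no stated blind classification, no stated relation to censoring and no statement of which dataset is primary. Against TAU, ascertainment can differ by arm. Between MBCT and CPE, the exposure is to unblinded reporting by the treating therapist.

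Direction and size cannot be determined from the document. The tabulated hazard ratios, from 0.79 to 1.16 when the truth is 1, are worst-case illustrations that rest on assumed detection rates and on outside data for all lost participants.

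A reader might also infer that the censoring and missing-data rules flatly contradict each other. They do so only if the last observation means the last blind SCID; otherwise this is an ambiguity to be resolved. This should be fixed, and it is a cheap improvement. It does not by itself undermine the design.

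**What to change.** Amend Appendix 1 to say:

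1. The primary Cox analysis uses relapse established by blind SCID assessment, plus return to treatment as judged by the blind rater, with censoring at the last such assessment.
2. GP information is used only if it is sought in the same way in all three arms, from each participant's own GP and not only referring GPs, and is classified and dated by a blind rater.
3. Therapist-sourced relapse data enter only the sensitivity analysis already planned, with a stated rule for how a report of no known relapse is handled.

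The cost is wording, plus slightly fewer events or less person-time in the primary analysis. The change should be made before anyone sees outcomes by arm.
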